### Study endpoint

The primary endpoint is to evaluate the incisional hernia rate at 3, 6, and 12 months after surgery in each group (study arm and control arm). The secondaries endpoints are to define morbidity (adverse events (AE) and serious adverse events (SAE)), surgery time, time to drain removal, length of stay in hospital, and mortality.

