#### Informed consent

All the criteria must be satisfied for included the patient in the study.

The exclusion criteria are:
Patients aged < 18 years oldInformed consent refusalNo clinical and/or laboratory and/or radiological evidence/signs of peritonitis of any originSurgical indication for laparotomies other than midline onePregnancy

The presence of even one of these exclusion criteria does not allow the patient to participate at the study.

The subject may withdraw at will at any time. The patient may be withdrawn from the trial at the discretion of the investigator for safety concerns. If the patient withdraws or is withdrawn at any time after receiving trial product, final safety information will be obtained. Patients who are deemed during surgery not suitable included in this protocol will be withdrawn from the study. In case a subject is being prematurely withdrawn from the trial, the investigator will ensure that the procedures for the last visit are undertaken, if possible. The primary reason (adverse event, non- compliance with protocol or other) for discontinuation must be specified in the CRF. A patient withdrawn from the study will be analyzed according to evaluability of subjects for analysis.

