### Visit procedures

The randomization and the study data are collected using an online form (https://prophybiom.easycrf.cloud). The access at this form is allowed only at the participant at the study that has a username and password. Investigators who conduct follow-up assessments will not be blinded.

The study comprises of the following visits (Table 1):

**Table 1 Tab1:** Time and event chart

Nomenclature	Visit 1	Visit 2	Visit 3	Visits 4, 5, and 6
	Screening	Treatment	Discharge	Follow-up
	Screening, baseline	Surgery	Discharge	Follow-up
**Informed consent**	**√**			
**Inclusion/exclusion criteria**	**√**			
**Demographic data (sex, age, weight, height, BMI)**	**√**			
**Medical history/concomitant illness**	**√**			
**Physical examination**	**√**		**√**	**√**
**ASA classification**	**√**			
**Vital signs**	**√**	**√**		
**Body weight and height**	**√**			
**ECG (12 lead)**	**√**			
**Hematology and coagulation parameters**	**√**		**√**	
**Blood chemistry**	**√**		**√**	
**Antibiotic therapy**	**√**			
**Start of LMW heparin**	**√**			
**Concomitant medication**^**a**^	**√ continuously**			
**Start and end of surgery**		**√**		
**Site and length of incision**		**√**		
**Peritonitis grade assessment**		**√**		
**Peritoneal fluid sampling for microbiological examination**		**√**		
**Contamination assessment**		**√**		
**Intestinal resection**		**√**		
**Stoma creation**		**√**		
**Surgical complications**		**√**		
**Surgical drain placement**		**√**		
**Surgery report**		**√**		
**Time of drain removal**			**√**	
**Length of stay in hospital**			**√**	
**Post-surgical complications**			**√**	**√**
**Abdominal wall ultrasound**				**√**
**Adverse events**	**√ continuously**			

^a^This includes use of any blood transfusions that should be inserted in the CRF as type (red blood cells. FFP, platelets)

• Visit 1: Screening and baseline visit: screening of patient, baseline examination, pre-surgery assessment, informed consent

• Visit 2: Treatment visit: surgery

• Visit 3: Discharge from hospital: recording of post-surgical complications

• Visits 4, 5, and 6: Post surgery follow-up visits: at 3, 6, and 12 months post-surgery. All patients will perform an abdominal wall ultrasound to document the presence or not of incisional hernia. At the last visit, the data collected is the same of the other visits. The patients are called 15 days prior to the follow-up visit to remind them of the appointment.

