### Statistical analysis

Only the data of participants who complete the follow-up will be considered. Descriptive analysis will be performed for all pre-operative, operative, and follow-up information. For categorical variables, we will use chi-square test, for non-categorical one the *t*-test. The primary endpoint, % of patients presenting incisional hernia at 3, 6, and 12 months, will be analyzed between treatment groups using a logistic regression model, presenting odds ratio comparisons of the two. Surgery time, time to drain removal and length of stay in hospital will be analyzed between treatment groups using Student’s *T* test if data are normally distributed and with Mann-Whitney test if data are not normally distributed. The distribution of data will be evaluated with the Shapiro-Francia test. The number of patients who died will be analyzed between treatment groups using a chi-square test.

All statistical comparisons will be based on two sided tests with a 5% significance level.

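### Length of stay and time to drain removal are compared only among patients who complete follow-up; the analysis set needs widening, together with a stated rule for in-hospital death

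*Protocol article*

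**What the plan says.** All references are to the protocol article.

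- **Study endpoint** lists as secondary, besides morbidity, "surgery time, time to drain removal, length of stay in hospital, and mortality".
- **Statistical analysis** sets the population in its first sentence: "Only the data of participants who complete the follow-up will be considered". It then states that "Surgery time, time to drain removal and length of stay in hospital will be analyzed between treatment groups" with Student's t-test if the data are normal and Mann-Whitney if they are not. Later it adds "The number of patients who died will be analyzed between treatment groups using a chi-square test".
- **Visit procedures** places follow-up "at 3, 6, and 12 months post-surgery". Table 1 there records time of drain removal and length of stay at Visit 3, the discharge visit.
- **Informed consent** (under Eligibility criteria) says "A patient withdrawn from the study will be analyzed according to evaluability of subjects for analysis"; the article does not define evaluability.
- **Abstract, Background** states that abdominal wall complications raise mortality and lengthen the hospital stay.

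**The concern.** Length of stay and drain time are complete, or cut short by death, within the index admission. Making them depend on completing follow-up, naturally read as reaching the 12-month visit, removes two groups:

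1. patients who die in hospital or before 12 months;
2. patients discharged alive, with both values recorded, who are later lost.

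Both exclusions happen after randomisation and can differ by arm. By the article's own account, the complication that the mesh is meant to prevent raises both mortality and stay. Removing the dead may therefore remove the patients who would have stayed longest, and more of them from the arm with more deaths. That arm could then appear to recover faster.

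The rule also cannot hold throughout the section. Among patients who survived to complete follow-up the number of deaths is zero by construction, so the mortality test must use another set. The article does not say whether stay and drain time follow the mortality test or the completers rule.

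**Working it through.** **The plan's own figure.** None is given for stay, drain time or expected mortality. The only figure used here is 45 per arm. It reproduces for 50% versus 20%, two-sided 5%, if power is taken as 80% (not stated) with continuity correction:

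- Uncorrected: n = [1.96·√(2·0.35·0.65) + 0.8416·√(0.5·0.5 + 0.2·0.8)]² / 0.30² = (1.3221 + 0.5389)² / 0.09 = 38.48.
- Corrected: (38.48/4)·[1 + √(1 + 4/(38.48·0.30))]² = 9.62·(2.1604)² = 44.9, so 45.

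This only sets the size of the simulated trials.

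**How many patients the rule removes through death alone**, at assumed mortalities: 10% of 45 is 4.5, 20% is 9 and 30% is 13.5. At 10% versus 30%, about 40.5 patients are compared with 31.5. Losses after discharge come on top; the article gives no rate for them and they are not modelled here.

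**Simulation, first set of assumptions** (none of these inputs is in the article):

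- 4,000 trials, 45 per arm, no treatment effect on stay.
- Stay if alive is log-normal, median 12 days, log-SD 0.6. Deaths fall uniformly on days 1 to 10.
- Frailty is either unrelated to death and stay, or related to both (correlation 0.7 with log stay; log-odds of death rising 1.5 per SD).
- Mann-Whitney, two-sided 5%.

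Cells give the difference in median stay in days (higher- minus lower-mortality arm; arbitrary where equal) and the rejection rate.

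| Mortality | Frailty | Completers only (as written) | All randomised, stay cut at death |
|---|---|---|---|
| 10% / 10% | unrelated | 0.00; 4.4% | +0.02; 4.3% |
| 10% / 10% | related | 0.00; 5.1% | -0.01; 5.3% |
| 10% / 20% | unrelated | 0.00; 5.1% | -0.99; 10.0% |
| 10% / 20% | related | -0.47; 6.4% | -1.19; 13.2% |
| 10% / 30% | unrelated | +0.04; 5.0% | -1.89; 22.7% |
| 10% / 30% | related | -0.88; 8.7% | -2.09; 38.0% |

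The Monte Carlo standard error near 5% is √(0.05·0.95/4000) = 0.34 percentage points.

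**Second set of assumptions** (median stay 14 days, log-SD 0.6, deaths at median day 5):

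- Completers only, odds of death rising with stay: the higher-mortality arm appears 0.83 days shorter at 10% versus 20% and 1.52 days at 10% versus 30%.
- All randomised, stay cut at death: median difference 0.99 days with 8.3% rejection at 10% versus 20%, and 2.15 days with 22.8% at 10% versus 30%. Rejection is 4.5% at 15% in both arms.

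**Deaths ranked worst** (first set). At 10% versus 30% the estimated probability that a lower-mortality patient ranks worse than a higher-mortality patient is 0.40 (frailty unrelated) or 0.43 (related), with rejection 38.0% and 23.2%. The direction is now right: the arm with more deaths ranks worse. These rejections reflect the mortality difference, not a difference in days.

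**The case against.** A reader might infer that the plan has no handling of in-hospital death at all, so that an early death counts as a short stay and the arm with more deaths gains about two days. The text does not support this. The completers sentence does handle deaths, by removing them, and a removed patient cannot contribute a short stay. The two-day and 23% to 38% figures describe an analysis that arises only if the completers rule is abandoned and nothing replaces it.

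Three further points limit the concern:

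- Both mechanisms as simulated need mortality to differ between arms. The article gives no expected mortality and no reason to expect a gap as wide as 10% versus 30%; Patients recruitment says no serious side effects of the prosthesis have been reported.
- Mortality has its own test and would be reported beside length of stay, which makes misreading less likely. No power claim rests on these secondary endpoints.
- A death rule for secondary durations is often left to a statistical analysis plan, and one may exist.

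The first two hold and limit the size. The third does not remove the point. The article is not silent: it fixes the tests and the population, and that population both selects after randomisation and makes another test in the same section impossible. A reader could rescue the section by treating a patient who dies as having completed follow-up. The article does not say so, and that reading brings back the problem of early deaths counted as short stays.

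**Conclusion.** The concern holds in limited form. As written, stay and drain time are compared among survivors who were retained, although both are known by discharge, and the same restriction rules out the comparison of deaths.

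The resulting bias in stay ranges from none, if frailty does not link death and stay, to about 0.9 days with roughly 9% rejection at an assumed 10% versus 30% mortality. A second set of assumptions, with odds of death rising with stay, gives 1.5 days. At equal mortality neither version of the analysis shows inflation. The article's Background makes a link between death and long stay plausible but does not quantify it, and nothing shows which arm, if either, would have more deaths.

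The practical point is that the obvious repair is not enough. Moving to all randomised patients under the stated tests gives a spurious advantage of about 1 day at 10% versus 20% and about 2 days at 10% versus 30%. The analysis set and the rule for death have to be changed together. This should be corrected, but it does not touch the primary endpoint.

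**What to change.** Replace the completers restriction for these two endpoints:

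- **Length of stay:** analyse all randomised patients by Mann-Whitney, with in-hospital deaths given the worst rank. Cumulative incidence of live discharge, with death as a competing event, is equally acceptable. State one in advance.
- **Time to drain removal:** analyse all patients who had a drain placed, whether or not they completed follow-up. Apply the same rule only to those who die with the drain in place, so that a removal time already observed is kept and patients without a drain are not assigned a value.
- **Descriptive addition:** report medians by arm among patients discharged alive.
- **Deaths:** state that the chi-square test is not limited to completers.

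The cost is wording in the protocol or analysis plan; Table 1 already collects stay and drain data at discharge. There are two downsides. The worst-rank result combines death and duration, is not a difference in days, and partly overlaps the mortality test. The drain comparison remains limited to patients with a drain: the Intervention section always places one over the prosthesis and describes none for the control arm, so the number with a drain should be reported by arm.

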### Data management

Data management is the responsibility of the principal investigator. All data relating to the various phases of the study will be collected in the appropriate electronic data collection form provided by an external company (m:gnu, Consultancy-Web Architecture-Management). The patients for whom the data is collected are cataloged with an identification code, which in the electronic version would translate into an alphanumeric code generated automatically by the system, thus avoiding the recording of personal data; in this way, the patient is de facto anonymized, and the data collected could not be considered “sensitive,” because they are not associated with an identifiable person. The cloud platforms that will be used are all GDPR compliant. The access at the anonymous data is permitted only at the principal investigator. The subject will be identified by subject number. Appropriate measures such as encryption or deletion will be enforced to protect the identity of human subjects in all presentations and publications as required by local/regional/national requirements. The data is monitoring by the principal investigator of the leader center of the study. There is a monitoring committee that monitors the data collection and study progress. This committee is the Unit of Clinical Research and Epidemiology of University Hospital of Parma. The monitoring committee monitors the data every 6 months. Statisticians, medical doctors specialized in epidemiology, and data managers are part of the monitoring committee.

When all 90 patients have been entered in the data base, data quality will be ensured and a data base release conducted.

## Discussion

To date, no randomized clinical trials have examined the efficacy of biological mesh in contaminated field, and no previous data exist on the efficacy of swine dermal collagen prosthesis in preventing incisional hernia in peritonitis patients.

Our randomized controlled trials have the aim to evaluate the impact of biological prosthesis in contaminated field, reduce the incidence of incisional hernia from 20 to 50%, and determine the impact on morbidity and mortality of the systematic swine dermal collagen prosthesis preperitoneal positioning.

The result of our study will increase the knowledge about swine dermal collagen prosthesis in peritonitis patients. The long follow-up of over 36 months would permit to understand the rate of incisional hernia in the medium-long term by comparing the patients treated with the biological prosthesis and those on which traditional treatment was performed. If the use of the swine biological prosthesis will prove to be an advantage (or disadvantage) in terms of reducing early and late post-operative complications (wound infections, seroma, wound dehiscence, bleeding, incisional hernia, re-surgery), it will probably be possible to draw up more precise guidelines in case of median laparotomies during surgery for peritonitis. In fact, the absence of clear indications on the approach in case of laparotomies on infected fields leads the surgeon to have random and different behaviors from case to case without determine the cause of possible post-operative complications.

Moreover, surgery performed in urgency for peritonitis is accompanied by a percentage of complications that are certainly higher than elective surgery. Trying to understand if it is possible to reduce the percentage of complications due to incisional hernias could also help to reduce the direct and indirect costs associated with surgery. Thus, studies that are aimed to determinate if it is possible are needed. The results of this trial will support a tangible decision-making process for choosing appropriate technical approach in abdominal parietal synthesis in peritonitis.

## Trial status

The trial was the winner of a grant from the Italian Ministry of Health for finalized research in 2018 (financial years 2016–2017) with project code RF-2018-12368001. This study in in phase IV. Patient recruitment has begun on 1 December 2020 and will end after 36 months on 1 December 2023.

## Data Availability

The data will be stored on an electronic database of University Hospital of Parma. The principal investigator will oversee the management of the final trial dataset. The study result will be used for oral presentation, publications, and seminars.
